# Clinical evaluation of ultrasonic subgingival debridement versus ultrasonic subgingival scaling combined with manual root planing in the treatment of periodontitis: study protocol for a randomized controlled trial

**DOI:** 10.1186/s13063-019-4031-y

**Published:** 2020-01-28

**Keywords:** Periodontitis, Non-surgical periodontal therapy, Ultrasonic subgingival debridement, Root planing

## Abstract

**Background:**

Periodontal diseases are regarded as the most common diseases of mankind. The prevalence rate of periodontal disease assumes a clear growth tendency, increasing by 57.3% from 1990 to 2010. Thereby, effective periodontal therapy is still a long-term task and a difficult problem. The goals of periodontal therapy are to eliminate the infectious and inflammatory processes of periodontal diseases. Root planing, in order to eliminate the “infected cementum,” has been an important step in the treatment of periodontitis since the 1970s. However, along with the understanding of the effects of endotoxin on the root surface, the necessity of manual root planing has been gradually queried. Ultrasonic instruments, which are more recent innovations, would not remove the cementum excessively, and are also more time-saving and labor-saving compared to using hand instruments. Hence, an increasing number of dentists prefer to do scaling with ultrasonic instruments only. However, the necessity of root planing remains emphasized in the international mainstream views of periodontal mechanical treatment. Therefore, this study is devoted to compare the clinical effect of ultrasonic subgingival debridement and ultrasonic subgingival scaling combined with manual root planing, which takes the implementation of root planing as the only variable and is more in line with the current clinical situation, thus hoping to provide some valuable reference to dentists.

**Methods/design:**

Forty adult patients who fit the inclusion criteria are being recruited from the Peking University Hospital of Stomatology (Beijing, China). By means of randomization tables, one quadrant of the upper and lower teeth is the test group and the other is the control group. Test group: ultrasonic subgingival scaling combined with manual root planing. Control group: ultrasonic subgingival debridement. In a 24-week follow-up period, plaque index, probing depth, clinical attachment loss, bleeding index, furcation involvement, mobility, and patient-reported outcome (Visual Analog Scale for pain and sensitivity) will be observed and documented.

**Discussion:**

This study evaluates the effectiveness of ultrasonic subgingival scaling combined with manual root planing and ultrasonic subgingival debridement alone in the nonsurgical treatment of periodontitis with a split-mouth design after 1, 3 and 6 months. The result of the trial should potentially contribute to an advanced treatment strategy for periodontitis with an ideal clinical outcome.

**Trial registration:**

International Clinical Trials Registry Platform (ICTRP), ID: ChiCTR1800017122. Registered on 12 July 2018.

## Background

Periodontal diseases are regarded as the most common diseases of mankind [1]. The prevalence rate of periodontal disease assumes a clear growth tendency worldwide, increasing by 57.3% from 1990 to 2010 [2–5]. The Global Burden of Disease Study [6] reports that periodontitis is the sixth most prevalent disease worldwide. The overall prevalence is 11.2% or around 743 million people in the worldwide. The prevalence of periodontitis in China is even higher. According to the recently released Fourth Epidemiologic Sampling Survey in China, the prevalence of periodontal disease is 90.9% in the age group of 35–44 years. Periodontitis is the main cause of tooth loss in the adult population worldwide that affects nutrition, quality of life and self-esteem as well as imposing great socio-economic impacts and healthcare costs [7–10]. However, good periodontal therapy is still a long-term task and a difficult problem. Periodontal treatment aims to control gingivitis and periodontitis, avoid disease progression leading to tooth loss, retain a functional dentition for a lifetime, preserve self-esteem and improve quality of life.

Subgingival plaque and calculus on the root surface in the periodontal pocket are the most important local factors for the occurrence and development of periodontitis. Hence, the ultimate goal of nonsurgical pocket/root instrumentation is to render the root free from microbial deposits and calculus. In the past, dentists used a variety of manual instruments (e.g., scalers, curettes) to remove these local irritants. Later, it was found that the vibration of ultrasonic tips, as well as the cavitation effect and microflow of cooling water could effectively remove plaque and calculus, which has made ultrasonic instruments widely used in nonsurgical treatment of periodontitis. These methods are collectively referred to as “subgingival scaling.” In the 1970s, Hatfield and Aleo found that endotoxin could penetrate to the cementum and influence the attachment of fibroblasts, leading to the concept of “root planing,” which means that the root surface should be smoothed by manual instruments to effectively remove the infected cementum, so as to remove endotoxin and form a smooth, hard and clean root surface with biocompatibility, which is conducive to the attachment and healing of periodontal tissue [11–13]. By the 1980s, more studies clarified that endotoxin was only loosely attached to the surface of the cementum [14, 15], and most of the endotoxin was related to the bacterial biofilm [16–18]. Therefore, it was suggested that excessive root planing for endotoxin removal was unreasonable. In 1994, the first European Working Conference on periodontology reached a consensus on the term “subgingival debridement,” that is, to use a gentle method to remove subgingival plaque and calculus, and to preserve the cementum as far as possible [19]. Ultrasonic instruments will not remove the cementum excessively, and are also more time-saving and labor-saving compared to hand instruments. Hence, an increasing number of dentists prefer to do scaling with ultrasonic instruments only. However, the necessity of root planing remains emphasized in the international mainstream views of periodontal mechanical treatment; ultrasonic subgingival scaling with manual root planing is recommended after supragingival scaling.

The primary objective of scaling and root planing is to restore gingival health by completely removing elements that provoke gingival inflammation (i.e., biofilm, calculus and endotoxin) from the tooth surface. A large amount of in vivo and in vitro research has been conducted to compare ultrasonic and manual instruments, and it was found that there was not much difference between them in clinical effects, changes in microflora and root surface characteristics [20–25]. In fact, there is still a lack of research evidence comparing the clinical effects of ultrasonic subgingival scaling with or without manual root planing. On the one hand, it is difficult to distinguish subgingival scaling from root planing in traditional manual operation; on the other hand, there are fewer dentists using manual subgingival scaling and root planing. Therefore, this study is devoted to comparing the clinical effect of ultrasonic subgingival debridement and ultrasonic subgingival scaling combined with manual root planing in the nonsurgical treatment of periodontitis, which, taking the implementation of root planing as the only variable, is more in line with the clinical situation, hoping to provide some valuable reference for dentists.

### Objectives and hypotheses

The major goals of the current randomized controlled trial are to compare and evaluate the clinical outcomes of ultrasonic subgingival debridement and ultrasonic subgingival scaling combined with manual root planing.

The primary hypotheses are root planing is an important step in nonsurgical treatment of periodontitis in order to remove subgingival plaque and calculus, eliminate the “infected cementum” and promote healing.

## Methods/design

### Overview

The study is a prospective, single-center, split-mouth randomized controlled trial. Forty patients who have periodontitis and are in need of periodontal treatment will be recruited. The assessments, interventions and follow-ups will be performed at Peking University School and Hospital of Stomatology (Beijing, China). This study has been approved by the Ethics Committee of Peking University School and Hospital of Stomatology (PKUSSIRB-201734032) and registered in the International Clinical Trials Registry Platform (ICTRP) under the ID: ChiCTR1800017122.

### Inclusion criteria

Aggressive periodontitis (AgP): according to the AgP diagnostic criteria established by the international symposium on the classification of periodontal diseases in 1999 [26]:
Aged 18 to 35 yearsRapid alveolar bone destruction and attachment loss: the probing depth of at least six teeth (at least three of them are non-first molars and incisors) in the whole mouth is greater than 5 mm, and the adjacent attachment loss is greater than 3 mm. All are confirmed to have alveolar bone resorption on the adjacent surface by examining periapical filmsThere are at least 20 remaining teeth in the whole mouth except the third molars, and at least one molar in each quadrant

Chronic periodontitis (CP): according to the CP diagnostic criteria established by the International Symposium on the Classification of Periodontal Diseases in 1999 specifies that [26]:
The patient’s onset age is between 35 and 60 yearsThe patient is systematically healthy, has gingival bleeding, swelling, pain, halitosis, teeth mobility and occlusive discomfortAt least one molar exists in each quadrant. At least two sites in each quadrant with a probing depth greater than 5 mm have attachment loss greater than 3 mmAt least 50% of all teeth in the whole mouth have the following conditions: (a) there exists sites with a probing depth greater than 5 mm; (b) alveolar bone absorption is greater than or equal to 30%; (c) there is bleeding on probing or periodontal abscessThere are at least 20 remaining teeth in the whole mouth except the third molars

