### Groups, randomization and blinding

An experienced periodontist is going to perform the periodontitis disease diagnostic process according to clinical and radiographic examination. The randomization sequence and allocation concealment (placed in sealed envelopes) were performed by a professor in the absence of the working investigators; one quadrant of the upper and lower teeth is the test group and the other quadrant is the control group. Test group: ultrasonic subgingival scaling combined with manual root planing. Control group: ultrasonic subgingival debridement. All subjects will be treated by one experienced and calibrated therapist who does not partake in the allocation, examination, or statistical analysis. The treatment plan and grouping will be confidential to the examiner and statistical analyst.

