### Primary parameters

The primary parameters of this trial are PD, CAL and BI.

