### Sample size

The sample size of this trial is calculated based on the formula:
$$ \kern13.25em N=\left[\frac{\left(z\frac{\alpha }{2}+ z\beta \right)\sigma }{\delta}\right]2\left(\frac{1}{Q1}+\frac{1}{Q2}\right). $$

According to the preliminary experiment results and data analysis from currently published articles, the difference of PD with and without root planing (*δ*) is around 0.3 mm and the standard deviation in groups (*σ*) is around 0.2 mm.

If the inspection level (*α*) is set at 0.05 and the power of test (*β*) is set at 90%, then 18 subjects will be required for each group. Given that loss to follow-up is around 10%, this study will require 20 subjects for each group. Consequently, this trial will require at least 40 subjects in all.

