### Statistical analysis

A Shapiro-Wilk test and Levene variance homogeneity test will be performed to test the normality and variance equality, respectively. Continuous normally distributed data will be expressed as mean ± standard deviation (SD), and non-normally distributed data as median (lower to upper quartile). A paired-samples *T* test or two-related-samples test will be used to identify any differences between groups. Statistical significance difference will be set as *P* value of less than 0.05. Data analyses will be performed using SPSS software.

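### The aggressive-periodontitis criterion secures no disease per quadrant, unlike the chronic criterion, so test and control quadrants can start clearly unequal and the paired difference becomes noisier

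*Protocol article*

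**What the plan says.** **Eligibility (Inclusion criteria).** The two diagnoses have separate lists.

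- Aggressive cases: extent is counted over the whole dentition, as "the probing depth of at least six teeth (at least three of them are non-first molars and incisors) in the whole mouth" with PD above 5 mm and adjacent attachment loss above 3 mm. At least 20 teeth must remain. The one condition set per quadrant is the presence of a molar, which concerns teeth and not disease.
- Chronic cases: every quadrant must hold two or more sites with PD above 5 mm and attachment loss above 3 mm, and at least half of all teeth must be affected.

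**Allocation (Groups, randomization and blinding).** The design is split-mouth: "one quadrant of the upper and lower teeth is the test group and the other quadrant is the control group". Each arm of a patient is therefore one upper plus one lower quadrant.

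**Outcomes and analysis.** "The primary parameters of this trial are PD, CAL and BI", with no restriction to deep sites. Under Statistical analysis, a paired-samples T "test or two-related-samples test will be used to identify any differences between groups".

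No section requires deep sites in both arms of an aggressive case.

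**The concern.** A split-mouth trial is efficient because the two arms of one mouth are alike at the start. The chronic criterion protects this by demanding disease in every quadrant. The aggressive criterion does not: six deep teeth may sit mostly, or wholly, in the quadrants that make up one arm.

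Two things follow for such a patient. First, PD and CAL can improve more where they start worse, so part of the test-minus-control difference reflects where the disease was and not whether root planing was done. Second, an arm with few deep sites has little room to improve. If that arm receives root planing, the patient can show almost no benefit from it. The first adds variance to the paired difference; the second weakens the contrast in the aggressive group.

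**Working it through.** **The plan's own figures.** The plan gives no figure on this point. Its sample-size inputs serve below only as a yardstick: the PD difference "is around 0.3 mm and the standard deviation in groups" "is around 0.2 mm", with alpha 0.05 and 90% power. The printed formula with Q1 = Q2 = 0.5 gives (1.960 + 1.282)² × 0.2²/0.3² × 4 = 18.68, close to the stated 18. Whether that is a total or a number per group is a separate matter and does not bear on this point.

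**1. What the aggressive criterion permits.** Without third molars a full quadrant has seven teeth, four of which are neither first molars nor incisors. All six required teeth can therefore lie in one quadrant with the at-least-three condition still met. Under the chronic criterion no quadrant can lack a deep site.

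**2. Illustration at the floor of the criterion.** Assumptions: 20 teeth, five per quadrant, exactly six deep, all placements equally likely, at-least-three condition ignored. An arm is any upper quadrant plus a lower one, so ten teeth. There are C(20,6) = 38,760 patterns.

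- One arm has no deep tooth: 2 × C(10,6) = 2 × 210 = 420; 420/38,760 = **1.1%**.
- One arm has at most one: 2 × [C(10,6) + 10 × C(10,5)] = 2 × (210 + 2,520) = 5,460; 5,460/38,760 = **14%**.

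**3. Sensitivity to the number of deep teeth** (at most one in an arm).

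- Eight deep: 2 × [C(10,8) + 10 × C(10,7)]/C(20,8) = 2 × (45 + 1,200)/125,970 = 2.0%.
- Ten deep: 2 × [1 + 10 × 10]/184,756 = 0.1%.

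**4. Cross-check on a full mouth.** Among 28 teeth, 303,744 six-tooth patterns meet the at-least-three condition. All six lie on one side in 28 + 15,120 × 2/6 = 5,068 of them, or 1.7%, in line with the 1.1% above.

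**5. Scale of the noise.** The documents do not say how much more deep teeth improve than others. Assume 1 mm of PD, range 0.5 to 1.5 mm.

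- A split of five against one over ten-tooth arms shifts that patient's difference by (5 − 1)/10 × 1 mm = 0.4 mm (0.2 to 0.6), against a planned effect of 0.3 mm.
- Under the random placement of step 2, the number of deep teeth in one arm has variance 6 × 0.5 × 0.5 × 14/19 = 1.105. The between-arm difference in counts has SD 2 × √1.105 = 2.10, so the added SD is 2.10/10 × 1 mm = 0.21 mm (0.11 to 0.32). This is about the size of the planned σ of 0.2 mm.

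**6. Against the plan's margin.** With 40 patients and 10% loss, 36 pairs remain. With no within-patient correlation, the SD of differences is 0.2 × √2 = 0.28 mm. If every patient were an aggressive case at the six-tooth floor, it would become √(0.28² + 0.21²) = 0.35 mm (0.30 to 0.42). By the normal approximation, 90% power is kept up to 0.3 × √36/(1.960 + 1.282) = 0.56 mm.

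**The case against.** **The lists may differ on purpose.** They describe two disease entities, and different extent rules are not a contradiction. That stands. But the per-quadrant rule for chronic cases suits the split-mouth comparison, which is the same for both diagnoses.

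**A reader might infer that some quadrants offer nothing to compare.** The documents do not support this. Every quadrant must hold a molar, the primary measures are not confined to deep sites, sites of 5 mm or less may still be diseased, and each arm pools two quadrants.

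**A reader might also cite how often some quadrant is empty.** In the model of step 2 that is [4 × C(15,6) − 6 × C(10,6)]/38,760 = 18,760/38,760 = 48%. The figure is correct but answers another question. The comparison is arm against arm, and an arm without any deep tooth occurs in 1.1% of patterns.

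**The harm is to precision, not validity.** This stands. Quadrants are randomised, so unequal disease favours neither arm systematically. On the plan's own σ, step 6 shows that 90% power survives even a pessimistic mix. That reassurance depends on σ = 0.2 mm being right.

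**The illustration takes the floor twice.** Both 20 teeth and six deep teeth are minima, and the figures fall quickly above them. Clustering on one side would raise them, and left-right symmetry would lower them. Neither is documented.

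**Little enrolment may remain.** Recruitment runs from October 2018 to June 2020 and the article is dated January 2020, so about five of some twenty months were left. This limits the reach of an eligibility change but not of an analysis change.

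**Conclusion.** The point holds as a matter of efficiency. The aggressive criterion lets patients enter with clearly unequal baseline disease between arms, which the chronic criterion guards against. At the floor of the criterion, under equal weighting, 14% of patterns leave an arm with at most one deep tooth and 1.1% with none. With eight or ten deep teeth the 14% falls to 2.0% or 0.1%. These are shares of permitted patterns, not expected patient frequencies.

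The result is added noise, plus a weaker contrast in aggressive cases with few deep teeth. It is not bias. The dilution is argued and not calculated. It reflects how few deep teeth an arm may hold more than asymmetry itself, since random allocation averages the asymmetry out. The overall effect cannot be computed, because the aggressive/chronic split and the distribution of disease are not given. The planned σ may also already contain some of this noise. Confidence is medium; the change is worth making because it is cheap.

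**What to change.** **Subjects still to be enrolled.** Reconcile the two lists so that the per-quadrant disease requirement (at least two sites with PD above 5 mm and attachment loss above 3 mm in each quadrant) also covers aggressive cases. The chronic list already needs quadrant-level probing at eligibility, so no new examination is introduced. The cost is an eligibility amendment, a few more screen failures and a slightly narrower aggressive group.

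**All subjects.** Keep PD, CAL and BI over all sites as the primary summaries, and adjust the within-patient comparison for the baseline value of each arm. One way is to regress each patient's test-minus-control difference at follow-up on the same difference at baseline and on the patient's centred baseline mean over both arms; the intercept is then the treatment effect at equal baseline. The baseline values are already collected, so the cost is a few lines of analysis text, fixed before allocation is revealed to the analyst.

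**Sensitivity analysis only.** Report the comparison on sites with baseline PD above 5 mm, in patients who have such sites in both arms. Making this the primary summary for those already enrolled would change the endpoint mid-trial, drop patients and split the primary analysis between earlier and later enrolees, so it is not proposed.

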### Exclusion criteria

Patients have received periodontal treatment within 6 months or taken antibacterial drugs within 3 monthsPregnant women or women of child-bearing age who do not take effective contraceptive measuresSystemic diseases such as cardiovascular and endocrine disease are presentAllergic to penicillinSmokers and those who cannot give up alcohol while taking drugsPatients do not agree to participate in the trial, and do not sign the informed consent

### Recruitment

Subjects who are looking for periodontal treatment and are willing to join this trial will be recruited from the Periodontology Department, Peking University School and Hospital of Stomatology. Subjects will receive the study information. Before subjects are included in the present study, the consent form must be signed. Figure 1 shows the flow procedure of participants through this trial.

**Fig. 1 Fig1:**
[figure not shown]
Consolidated Standards of Reporting Trials (CONSORT) diagram

### Groups, randomization and blinding

An experienced periodontist is going to perform the periodontitis disease diagnostic process according to clinical and radiographic examination. The randomization sequence and allocation concealment (placed in sealed envelopes) were performed by a professor in the absence of the working investigators; one quadrant of the upper and lower teeth is the test group and the other quadrant is the control group. Test group: ultrasonic subgingival scaling combined with manual root planing. Control group: ultrasonic subgingival debridement. All subjects will be treated by one experienced and calibrated therapist who does not partake in the allocation, examination, or statistical analysis. The treatment plan and grouping will be confidential to the examiner and statistical analyst.

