### Interventions

All enrolled subjects received supragingival scaling using ultrasonic scalers, oral hygiene instruction (OHI) including tooth brushing with the modified Bass technique and interdental cleaning with interdental brushes or dental floss. They are submitted to a complete periodontal clinical assessment. Subsequently, the upper and lower teeth of each subject are randomly allocated to the following therapeutic groups: (1) ultrasonic subgingival scaling combined with manual root planing group; (2) ultrasonic subgingival debridement group. The treatment is carried out at the Periodontology Department, Peking University School and Hospital of Stomatology. The treatment is performed by an experienced periodontist who has been calibrated before the trial. The treatment is completed under local anesthesia in two sessions of approximately 1 h, distributed over a period of 7 days. Ultrasonic subgingival scaling is performed using magnetostrictive ultrasonic device (Charlotte, North Carolina Dentsply, model number: Gen-130B, 25 kHz, USA). Manual root planing is performed using Gracey curettes (conventional and mini-fives) numbers 5/6, 7/8, 11/12 and 13/14 (Hu-Friedy, Shanghai, China). At the end of each session, the clinical coordinator evaluates the effectiveness of treatment using the outcome “smoothness of the scaled roots.” All subjects will receive personalized OHI after treatment until the end of the study (24 weeks post therapy).

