## Discussion

Periodontitis is strongly associated with the presence of bacterial biofilms and dental calculus on root surfaces. Hence, the ultimate goal of nonsurgical pocket/root instrumentation is to render the root free from microbial deposits and calculus. The success of periodontal treatment depends on the removal of deposits from the root surface [27–30]. All kinds of studies performed in different models and under different conditions have indicated that neither manual nor mechanical instruments are superior in removing subgingival deposits [31–37]. There was no significant difference in the changes of PD, CAL and BOP between manual subgingival debridement and ultrasonic subgingival debridement.

Previous studies demonstrated that hand instrumentation curettage created the smoothest root surface, whereas mechanical instruments, such as the ultrasonic scaler, tended to roughen the root surface [38]. Cobb found that manual curettes were more technique-sensitive and time-consuming [39]. The old concept of infected cementum removal in order to provide the root surface biocompatible for soft tissue healing [11, 12] has been questioned by various studies [15, 16]. The utilization of ultrasonic devices for subgingival debridement offers a less aggressive and a more comfortable therapeutic method for both the patient and therapist. But, some research has shown that the comparison between manual instruments and ultrasonic scalers did not show an advantage over machine-driven instruments [20], and tissue trauma was similar in both instruments [40]. Therefore, the necessity of manual root planing cannot be completely denied. Hand instrumentation has been recommended to smooth the root surface after ultrasonic debridement as the final finishing procedure in the treatment of periodontitis-affected roots [41]. At present, root planing is no longer used to emphasize the deliberate removal of cementum, but to contribute to the removal of subgingival plaque.

This study thus intends to evaluate in vivo the effectiveness of ultrasonic subgingival scaling combined with manual root planing and ultrasonic subgingival debridement alone in the nonsurgical treatment of periodontitis with a split-mouth design after 1, 3 and 6 months. We hope that the results could lead to an advanced treatment strategy of periodontitis with an ideal clinical outcome.

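### The protocol does not secure its claim that root planing is the sole difference between arms: allocation can be known during the shared ultrasonic step, and the one stated quality check is not neutral between arms

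*Protocol article*

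**What the plan says.** The isolation claim appears twice in the protocol article. The abstract's Background says the study "takes the implementation of root planing as the only variable", and the main Background repeats it as "taking the implementation of root planing as the only variable".

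On delivery, the section Groups, randomization and blinding says: "All subjects will be treated by one experienced and calibrated therapist who does not partake in the allocation, examination, or statistical analysis". On concealment it says: "The randomization sequence and allocation concealment (placed in sealed envelopes) were performed by a professor in the absence of the working investigators". On blinding it says: "The treatment plan and grouping will be confidential to the examiner and statistical analyst". The therapist is not among those kept unaware.

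The Interventions section sets out an order: supragingival scaling and hygiene instruction, then the clinical assessment, then "Subsequently, the upper and lower teeth of each subject are randomly allocated to the following therapeutic groups", and after that the subgingival treatment in two sessions of about 1 h within 7 days. At the end of each session "the clinical coordinator evaluates the effectiveness of treatment using the outcome" of how smooth the scaled roots are.

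The Discussion reports from earlier studies that "hand instrumentation curettage created the smoothest root surface, whereas mechanical instruments, such as the ultrasonic scaler, tended to roughen the root surface".

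**The concern.** The arms are ultrasonic instrumentation alone and ultrasonic instrumentation followed by manual root planing. The contrast equals the effect of planing only if the ultrasonic part is the same in both. In a split-mouth trial one operator works on both arms in the same mouth. If that operator knows which quadrants will be planed, the ultrasonic work can drift in two ways: more of it where no curette will follow, which shrinks the contrast, or less of it where planing will finish the job, which could also shift the contrast.

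The blinded examiner measures the result accurately in either case but cannot tell a planing effect from a difference in ultrasonic effort, and no analysis of the listed outcomes can separate them. A quality check that rewards the product of the step under test adds a reason for the two arms to be handled differently.

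**Working it through.** The point turns on no figure in the plan, so there is none to reproduce. The passages are set side by side.

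1. *What the claim requires.* Both Background texts say planing is all that varies. This requires equal delivery of the ultrasonic step.

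2. *Who knows the allocation.* Whoever planes must know which quadrants to plane. Groups, randomization and blinding lists the examiner and the analyst as unaware, and no one else.

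3. *When it is known.* Interventions describes allocation after the assessment and before subgingival treatment. Sealed envelopes are mentioned, but not the moment of opening. On this text, knowledge of the allocation during the ultrasonic step is possible and is the natural reading of the order, but it is not stated.

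4. *What holds the ultrasonic step constant.* The device is named and the therapist is calibrated. The only time given is the two sessions of about 1 h, which is not split by arm or by step. Nothing described fixes ultrasonic effort per quadrant.

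5. *What the quality check measures.* Interventions rates the effectiveness of treatment by root smoothness. The Background explains root planing as smoothing the root surface with manual instruments, and the Discussion says curettes give the smoothest surface while ultrasonic scalers tend to roughen it. By the article's own account, the check follows the step that defines the test arm. It is applied to both arms, and the text does not say what follows from a poor result.

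*Illustration, not an estimate.* How much uneven effort would matter depends on assumptions.
- Inputs from Sample size: standard deviation in groups 0.2 mm; two-sided α 0.05; 40 subjects, or 40 × 0.9 = 36 after 10% loss.
- Assumptions not in the protocol: 0.2 mm is the SD of each arm's patient-level probing depth; one paired t test is done on 36 to 40 patients; the within-patient correlation ρ is 0 to 0.5; planing has no effect; uneven ultrasonic work alone creates a difference b.
- SD of the paired difference = 0.2 × √(2(1 − ρ)): 0.283 mm at ρ = 0 and 0.200 mm at ρ = 0.5.
- Standard error = SD/√n; noncentrality = b/SE; chance of P < 0.05 from the noncentral t distribution.

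| n | ρ | SE (mm) | b = 0.05 mm | b = 0.10 mm |
|---|---|---|---|---|
| 36 | 0 | 0.0471 | 18% | 54% |
| 36 | 0.5 | 0.0333 | 31% | 83% |
| 40 | 0 | 0.0447 | 19% | 59% |
| 40 | 0.5 | 0.0316 | 34% | 87% |

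On the plan's own SD, a spurious difference of one sixth (0.05/0.3) to one third (0.10/0.3) of the assumed 0.3 mm effect would be declared significant in about 18% to 34% and 54% to 87% of trials respectively. Nothing in the document says that a difference of this size will arise.

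**The case against.** An unblinded operator is unavoidable once planing starts, and the article controls much of what can be controlled: one calibrated therapist with no part in allocation, examination or analysis, and a blinded examiner and analyst. The sentence about the therapist is a safeguard and contains no error. The time of opening an envelope is also an operational detail that an article may leave to the full protocol. All of this stands. It limits the point to the shared step that comes before planing, where concealment is feasible and where blinded examination gives no protection.

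A reader might go further and infer three things that the document does not support.

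- *That the therapist does know the allocation during the ultrasonic step.* The order in Interventions suggests this, but the envelope could be opened later.
- *That smoothness decides when treatment is complete, so that control quadrants fail by construction.* The text says the coordinator evaluates effectiveness. It gives no threshold, stopping rule or re-treatment rule, and the Discussion says only that ultrasonic scalers tend to roughen roots.
- *That planing is therefore shown not to be the only variable.* The Background describes the intended contrast. A possible departure in delivery means the claim is not assured; it does not show it to be false.

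Nor can a definite loss of power be claimed. The document gives neither the amount by which the contrast might shrink nor the SD of the paired difference.

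**Conclusion.** The point holds in a limited form. As described, the trial does not assure that root planing is the only difference between arms. The therapist can know the allocation during the shared ultrasonic step, and the one stated quality check measures a property that the article itself ties to hand instruments. The bias could go in either direction, and its size cannot be estimated from the document. The percentages in the working show only how sensitive the comparison would be under the stated assumptions.

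This goes beyond a missing detail, because a cheap change of sequence would close a route to performance bias that blinded examination cannot correct. The conclusion rests on reading the order in Interventions as the order of events. If the full protocol already delays disclosure until the ultrasonic work is done, the first part falls away and only the question about the smoothness check remains.

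**What to change.** 1. Open the sealed envelope only after the ultrasonic instrumentation of all quadrants scheduled for that session is finished, and state this in the protocol.
2. Schedule test and control quadrants in the same session, so that arm is not tied to session and the delayed opening covers both arms. The article does not give the session layout, so this may already be the practice.
3. Reconcile the smoothness check in Interventions with the definitions of the two arms and with the Discussion. State its purpose and what, if anything, follows from it, and record its result by arm. What it should lead to is for the investigators to decide.
4. For subjects treated with the allocation known during the ultrasonic step, soften the only-variable wording in the report and name uneven ultrasonic delivery as a limitation.

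Cost: somewhat less scheduling freedom for the therapist and one more recorded item per session, with no extra visits or staff. Recruitment began in October 2018 and the intervention period was due to end in June 2020, so items 1 and 2 can reach only subjects not yet treated. Item 4 covers the others.
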